**Index**

**1. Introduction**....................................................................................... .......... **p 2**

**2. Rational**............. ....................................................................... **p 3**

**3. Aims of the study**........................................................................ .............. **p 5**

**4. Diagnosis of early onset nosocomial pneumonia** ............................. **p 6**

**5. Treatments**.................................................................................................. **p 7**

**6. Patients**......................................................................................................... **p 9**

**7. Evaluation criteria ……….**.............................. **p 11**

**8. Timing**................................................................................ …**p 14**

**9. Organisation**...................................................................... …**p 16**

**10. Secondary aims**.............................................................................. . **p 18**

**11. Statistical analysis**......................................................................  **..p 21**

**12. Results**.............................................................................. ..**p 23**

**Appendices**..................................................................................... … **p 24**

**References……**...............................................................................................**p 41**

1. Introduction

Nosocomial Pneumonia is defined as an infection of the lung parenchyma acquired in the hospital, which means that it was neither present nor in incubation at admission (criteria defined by the Center for Disease Control) (12). Nosocomial pneumonia is the third most prevalent cause of nosocomial infection, representing about 15% of infections acquired in hospital (17). Their prevalence among patients varies between 1% and 20% respectively in medical and critical care units (8). Intubation and mechanical ventilation are recognized risk factors for the acquisition of nosocomial pneumonia (15). Among all nosocomial infections, nosocomial pneumonia is associated with the highest mortality rate. Mortality is higher than 50% in ventilated patients (9). Their frequency and severity, pose a real public health problem, particularly in intensive care units.

Despite the difficulty of accurately assessing morbidity and the additional cost, some studies clearly show that nosocomial pneumonia is at the origin of complications (septic shock, infections...) and results in an extension of stay in many ventilated patients (9.16)

2. Rational of the study

Early onset nosocomial pneumonia will be defined by a new occurrence of pulmonary infection on mechanical ventilation in the first 8 days of ventilation and on the profile of antibiotic susceptibility of the microorganism (sensitivity retained to 3rd generation cephalosporins and aminoglycosides). In early onset nosocomial pulmonary infection, bacterial flora normally found consists of Haemophilus Influenzae, Streptococcus Pneumoniae, Staphylococcus Aureus, Methicillin-sensitive, Moraxella Catarrhalis, Escherichia Coli (1,7,24).

This study of early nosocomial pulmonary infection will likely restrict findings to "community", non-multi drug resistant microorganisms and patients without multiple infections. This option is available to obtain homogeneous groups from the infectious point of view and to standardize the evaluation criteria.

**2.2 Duration of treatment**

As a general rule, the duration of antibiotic treatment of pulmonary infection is rarely addressed, except for a few specific pathologies (e.g. Mycobacterium tuberculosis). It is interesting to note that the different consensus of Infectious Pathology conferences and pharmacological and microbiological textbooks regularly conflict over the duration of the anti-infective treatment (19). The duration of antibiotic treatment is still empirical, available data is fragmentary and studies that investigate antibiotic therapy are not specifically exploring the duration of the treatment. The duration of treatment of community acquired pulmonary infection varies between 5 and 14 days according to the author choice (22), or even 3 days using newer drugs with longer half-lives (2). For nosocomial pulmonary infection, treatment durations are not standardized (5). It is simply mentioned the concept of "usual" treatment of at least 15 days. However, recent studies used 10 days of treatment without significant decrease in disease resolution compared to usual treatment (6,10,31).

It is essential to clarify the optimal duration of antibiotic treatment. Indeed, any excessive extension of treatment may increase the occurrence of adverse effects (renal toxicities, hepatic...), and induce resistance of bacteria to antibiotics (selection pressure), colonization of the patient by multi-resistant bacteria and an increase in cost of treatment (13).

**2.3 Treatment modalities**

Some studies show the possibility of treating pulmonary nosocomial disease with monotherapy, particularly with the newer drugs (10.18). However, most authors agree that it is still preferable to use a combination of antibiotics in the treatment of nosocomial pulmonary disease (1). This therapeutic attitude aims to broadening the antibiotic spectrum (especially when intitiating the treatment), and provide a synergystic effect in order to accelerate the bactericidal effects and decrease the emergence of resistant microrganisms. The concurrent use of beta lactams and aminoglycosides is justified as we excluded the new broad spectrum antibiotics from the protocal.

The use of high dose beta-lactam antibiotics is justified by the existence of an important bacterial load in nosocomial pulmonary infection (26) and by the changes (increase in the volume of distribution) pharmakokinetic observed in the resuscitated patient (3). High dose antibiotic therapy in the first 3 days, was recently being described in the treatment of community pulmonary infection requiring hospitalization (4).

The rational for once daily administration of aminoglycosides is multiple: clinical efficacy, toxicity, gain of nursing time and potential reduction of costs (20). All clinical studies show an equivalent efficiency for the three modes of administration of aminoglycosides (1, 2 or 3 injections per day), without change of the level of toxicity (14). Some authors (29) observe a better renal tolerance of the netilmicine administered in a single dose. The pharmacokinetic study of the aminoglycoside antibiotics administered in a single dose in the critical care patient highlights a decrease of 15 to 35% of the peak plasma concentration, compared to that observed in healthy volunteers (21). This phenomenon is due to the increase in the volume of distribution (3). These arguments support the case for a higher loading dose of 25-30% (28) and an increase of the daily dose when injected as a single daily dose.

**3. Objectives of the study**

**This is a prospective, randomized, open, multi-center study.**

**3.1 Primary Objective**

To show that antibiotic therapy of 8 or 15 days is equivalent in terms of clinical cure rates in the treatment of early onset nosocomial pulmonary infection in patients receiving mechanical ventilation.

- 1. **Secondary Objective**

**. Study of nosocomial infections:** assessing the influence of the duration of antibiotic treatment on the rate of potentially fatal pulmonary and extra-pulmonary infection (definition of nosocomial infections: annex XIII).

- **Study of bacterial Ecology:** research of changes in the flora of the gut under treatment and analysis of pathological samples (antibiotic resistance phenotypes +/- genotypes).

**. Economic Survey:** analyze the costs related to the treatment of nosocomial pneumonia and its complications in the two study groups.

**4 Diagnosis of early onset nosocomial infection**

The diagnosis of early onset ventilator associated pneumonia is confirmed if all of the following criteria is met:

**4.1 Clinical signs**

- artificial ventilation started since at least 24 hours and for less than 8 days

- 2 of 3 following criteria: temperature (>38.5 ° C or (<36 ° C), leukocytosis (>12 000 / mm3 or (<5 000 / mm3), abundant, purulent or mucopurulent sputum

- absence of another focus of infection documented the day of the BAL

**4.2 Radiological criteria**

- increase of 2 points in the radiological score from chest radiography done on admission (annex I)

**4.3 Bacteriological results**

- quantitative culture of bronchoalveolar lavage (BAL) greater than 104 cfu / ml (Appendix II)

**5. Treatment**

**5.1 Intitiating the treatment**

A BAL will be made upon suspicion of nosocomial pneumonia (clinical and radiological criteria defined in Section 4). Patients will be treated either after the BAL bacteriological results, or immediately after the BAL according to the predefined severity criteria (Appendix III). If the antibiotic treatment is started immediately after the BAL, the patient will be included in the study as long as the treatment is not changed after the results of the sensitivity.

**5.2 Treatment**

All patients included in the study will be treated by a combination of antibiotics during the first 5 days (Beta-lactam + Aminoglycoside), then by monotherapy (Beta-lactam alone) for 3 or 10 days according to the group. The beta-lactam antibiotics will be administered in high doses during the first 3 days of treatment. Aminoglycosides will be administered as a single daily dose, with a loading dose administered on the first day of treatment. The patient will remain hospitalized (intensive care units or other units) for the duration of the treatment.

Definition :

- J0 = introduction of treatment whatever the time is
- J1 = first full day of treatment
- J4 = decrease in the dose of beta-lactam antibiotics, after 3 full days of treatment with high dose antibiotics; intermediate evaluation will be performed
- J6 = Stop aminoglycosides, after 5 full days of treatment
- J9 = Stop beta-lactam antibiotics in the "short" arm.
- J16 = Stop of the beta-lactam antibiotics in the "long" arm.
- J21 = Final evaluation.

**5.3** **Authorized antibiotics in the study**

**- Beta-Lactams**

- Amoxicillin + clavulanic Acid : **2 g TDS for 3 days, then 1 g TDS**
- Keftriaxone : **2 g OD during 3 days, then 1 g OD**
- Kefotaxime : **2 g TDS during 3 days, then 1 g TDS**

**- Aminoglycosides**

- Tobramycin : **loading dose of 6 mg/kg OD, then** **5 mg/kg OD (adaptation in case of renal failure)**
- Netilmicin : **loading dose of 10 mg/kg OD, then** **8 mg/kg OD (adaptation in case of renal failure)**
- Dibekacin : **loading dose of 6 mg/kg OD, then** **5 mg/kg OD (adaptation in case of renal failure)**

**5.4** **Non-authorized antibiotics in the study**

All other antibiotics, outside those proposed in the protocol, will not be used in the initial treatment.

**5.5** **Antibiotic adjustment**

If a new pulmonary or non pulmonary superinfection develops, all antibiotics are usable, supported by bacteriological data. Any change of antibiotic treatment for new pulmonary infection occurring after the beginning of the protocol has to be supported by a BAL if the patient is intubated.

**6. Patients**

**6.1 Inclusion criteria**

- Early onset nosocomial pneumonia (delay in onset is less than or equal to 8 d of artificial ventilation), in patients under mechanical ventilation for at least 24 h

- Patients aged 18 years or more

- The patient must be able to receive either one of the two arms of treatment defined for the study

- Information will be given to the patient and his family and informed consent will be obtained during the first three days: through family if the patient is incapable of giving consent.

- Microorganisms (s) sensitive to the specified antibiotic regimen (ref 5.3)

**6.2 Exclusion criteria**

- Patients do not match the criteria for inclusion

- Patients aged under 18 years of age

- Pregnant patients

- Another infectious outbreak documented the day of the BAL.

- Patients with acquired (blood diseases, HIV,...), induced (immunosuppressive drugs, cancer, radiation therapy) or congenital immunosuppresion.

- Steroids for a period exceeding 15 days.

- Leukopenia (1000 GB/mm) or neutropenia (500 PN/mm)

- Purulent pleural effusion, pulmonary abscess

- Cystic fibrosis

- Patient previously receiving antibiotic treatment according to the following terms:

1. Ongoing curative antibiotic therapy

2. Antibiotics within 3 days before the diagnosis of VAP, excluding surgical antibiotic prophylaxis (defined according to the consensus conference "antibiotic prophylaxis in the surgical environment in adult" December 11, 1992) (27)

3. Use of antibiotics not authorized in the study (see list)

- Allergy to antibiotics used in the study

- Inclusion in another study assessing antibiotic treatment, either the treatment or prevention of nosocomial pulmonary disease

- Refusal to participate

- Lack of informed consent by the patient or his family

**7. Criteria of evaluation of the main objective**

**7.1 Parameters to define the clinical response :** highest temperature over 24 hours for hyperthermia or lowest in case of hypothermia ; leukocytosis (morning sample) character of bronchial secretions ; chest X-ray (radiological score: Appendix II) ; PaO2/FiO2 ratio (in a stable situation, outside intercurrent acute events)

**7.2 Main judgment Criteria**

The main criterion of judgment is the clinical response.

**7.2.1 Failure ;**

- Death for what ever reason during the protocol

- Initial clinical worsening judged after D3 of treatment:

septic shock (Appendix IV) or "sepsis syndrome" (Score of organ failure related to sepsis: SOFA Appendix V) without another documented infection - increase in the score of organ failure (increase in SOFA score by 2 points or more) with identification of the same microorganism at a new BAL

- Persistence or increase of all signs of pulmonary infection after D3 of treatment:

- temperature > 38.5° or < 36 °

- > 12000 WBC / mm3 or < 5000 / mm3

- purulent bronchial secretions

- absence of pulmonary radiological improvement and persistence of the original microorganism in the BAL

- A need to change the initial antibiotic for treatment intolerance (Appendix VI)

If failure is diagnosed, regardless of the day (After D3 of treatment), the patient is assessed as failure in the final evaluation at D21.

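### Failure by persistence requires every listed sign, but entry requires only two of three clinical signs, so an unchanged two-sign entrant cannot meet this criterion and may be left unclassified or later scored a cure

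*Protocol*

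**What the plan says.** **Entry (Protocol, section 4).** The clinical part of the diagnosis is "2 of 3 following criteria: temperature (>38.5 ° C or (<36 ° C), leukocytosis (>12 000 / mm3 or (<5 000 / mm3), abundant, purulent or mucopurulent sputum". Sections 4.2 and 4.3 add two compulsory elements: "increase of 2 points in the radiological score from chest radiography done on admission" and "quantitative culture of bronchoalveolar lavage (BAL) greater than 104 cfu / ml".

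**Failure (section 7.2.1).** There are four routes: "Death for what ever reason during the protocol"; "Initial clinical worsening judged after D3 of treatment", which is defined by septic shock, sepsis syndrome or a rise in organ-failure score with the same organism; "Persistence or increase of all signs of pulmonary infection after D3 of treatment"; and a change of the initial antibiotic for intolerance. The persistence route repeats the three clinical signs, with the same cut-offs for temperature and leukocytes, and ends with "absence of pulmonary radiological improvement and persistence of the original microorganism in the BAL". Failure is then irreversible: "If failure is diagnosed, regardless of the day (After D3 of treatment), the patient is assessed as failure in the final evaluation at D21".

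**Cure (section 7.2.2).** Cure is judged at D21. For intubated and extubated patients alike it requires, among other things, non-purulent or absent secretions and a chest film that is normal or has improved by at least 2 points since D0. The schedule in section 8 gives the D21 evaluation two outcomes, failure or cure. Section 11.1 makes the cure rate at D21 the main criterion.

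**The concern.** The entry rule and the persistence rule use the same three clinical signs but count them differently: two suffice to enter, and all three are needed to fail by persistence. Nothing in section 7.2.1 limits the word all to the signs that a patient had at the start.

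Two patients at the D16 evaluation show the effect. Patient A entered with fever, purulent secretions and 10 000 leukocytes. He now has 39.2°, purulent secretions, 11 000 leukocytes, no radiological improvement and the same organism in the BAL. Patient B entered with all three signs and is now identical to A except for 12 500 leukocytes. Nothing has resolved in either patient. B is a failure and stays one to D21. A is not a failure by this criterion.

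The classification of the main criterion is at stake. In a trial that seeks to show equivalence within 10 points, failures that go unrecorded in both arms can bring the arms closer together.

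**Working it through.** The protocol gives no figure on this point, so the main check is logical.

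**1. The rules side by side**

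| Element | Entry (4.1–4.3) | Failure by persistence (7.2.1) |
| --- | --- | --- |
| Temperature | one of three, two needed | needed |
| Leukocytes | one of three, two needed | needed |
| Secretions | one of three, two needed | needed (purulent) |
| Chest film | needed | no improvement needed |
| Organism in BAL | needed | same organism needed |

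**2. Entry profiles.** Four combinations of temperature, leukocytes and secretions satisfy section 4.1: all three signs, or one of the three possible pairs. Hold each unchanged after D3, with no radiological improvement and the same organism.

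- Literal reading, every listed sign required: 1 of 4 profiles meets the criterion. The three pairs do not.
- Reading limited to the signs present at entry: 4 of 4 meet it.

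**3. A two-sign patient still unchanged at D21.** Persistence is not met. Worsening is not met, because nothing has worsened. Cure is not met, because the film is neither normal nor better by 2 points. The patient is in neither category of section 7.2, while section 8 allows only two outcomes. No sentence says that a patient who is not cured counts as a failure.

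**4. A two-sign patient re-treated before D21.** Section 7.2.1 counts an antibiotic change as failure only when the reason is intolerance. Section 7.3 covers a new BAL that is sterile or grows a different organism; it is silent on the same organism. Only the Home rule in section 7.2.2 bars cure after a new antibiotic for lung infection; the lists for intubated and extubated patients do not. In hospital, such a patient can therefore meet the cure list at D21. The matching three-sign patient cannot, because of the lock-in.

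**5. When this can differ between arms.** Under section 5.2 the planned treatment is the same in both arms until J9. Misses before J9 should fall equally on both arms. Only persistence after J9 can carry an effect of the shorter course.

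**6. Illustration of size (assumed inputs).** Suppose that each clinical sign is present independently with probability p. The share s of entrants with exactly two signs is

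s = 3p²(1−p) / [3p²(1−p) + p³] = 3(1−p) / (3−2p).

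Apply this to the 280 included patients in the last row of the table in section 11.2. Suppose also a true 15-point excess of persistent infection in the short arm, acting wholly through this criterion, and let c be the fraction of missed patients later scored cured. The counted excess is 15 × (1 − s·c).

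| p | s | s × 280 | c = 1 | c = 0.5 |
| --- | --- | --- | --- | --- |
| 0.9 | 0.3/1.2 = 25% | 70 | 11.3 | 13.1 |
| 0.8 | 0.6/1.4 = 43% | 120 | 8.6 | 11.8 |
| 0.7 | 0.9/1.6 = 56% | 158 | 6.6 | 10.8 |

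The counted excess falls below 10 points only if s·c exceeds 1/3. At p = 0.9 that cannot happen (0.25 × 1 = 0.25). At p = 0.8 it needs c above 0.333/0.429 = 0.78, and at p = 0.7 above 0.333/0.5625 = 0.59.

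**The case against.** **The patient is not cured anyway.** The main criterion is the cure rate, and someone who stays unchanged to D21 is not a cure on any reading. This stands, and it confines the possible bias to patients who are re-treated and then meet the cure list. It does not settle how the unchanged patient is recorded.

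**A sign can persist only if it was there.** On that view, all signs means those present at entry, and the mismatch disappears. The reading is sensible, but the section gives fixed thresholds without reference to baseline. In an open, multi-centre trial, two tenable readings of a main-endpoint rule need a sentence to decide between them.

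**A strict rule suits an irreversible label.** This is fair, and it argues against applying a flat two-of-three rule after D3, which would lock in as failures patients who entered with three signs and have resolved one.

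**The bias depends on another gap.** Without the silence on re-treatment for the same organism, patient A could not become a cure. That is correct. Section 5.5 speaks only of new superinfection, so the protocol does not describe such re-treatment; it does not exclude it from the cure count either. Aligning the signs narrows this gap without closing it.

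**Stronger readings.** A reader might infer that a two-sign entrant can never be a failure. The documents do not support that: death, septic worsening and intolerance apply to everyone, and a patient who later acquires the third sign can meet the persistence rule. A reader might also infer that a 15-point excess would be hidden inside the margin. The protocol supplies none of the inputs for that claim, and with half of the missed patients later scored cured, all three results stay above 10 points.

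**Conclusion.** The mismatch between sections 4.1 and 7.2.1 is real. On the literal text, an unchanged two-sign entrant cannot fail by persistence and so escapes the lock-in. Two consequences follow: a patient unchanged at D21 has no defined outcome, and a patient re-treated in hospital can be scored a cure of the assigned duration when a three-sign counterpart cannot. After J9 the second consequence can dilute a difference between arms towards equivalence.

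The size is unknown, because the protocol does not give the share of two-sign entrants. For each assumed share, the figures of 11.3, 8.6 and 6.6 points show the largest dilution, with every missed patient later scored cured. They also assume independent signs, equal persistence risk in two-sign and three-sign entrants, and a 15-point excess acting only through this criterion after the arms diverge. They show a direction and are not an estimate. The point is an inexpensive repair to an endpoint definition; it does not show that the trial's conclusion would be wrong.

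**What to change.** Reconcile section 7.2.1 with section 4.1 in two sentences:

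- Define the criterion as persistence or increase, after D3, of all the clinical signs of section 4.1 that were present at entry, together with no radiological improvement and the original organism in the BAL.
- State that a patient who meets neither the failure nor the cure definition at D21 counts as not cured.

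Both sentences concern classification only and leave treatment untouched. The signs are among the parameters already named in section 7.1 and the entry criteria, so no new data are needed. The expected cure rate may be slightly lower in both arms, which should be kept in mind when the 80 to 90% range in section 11.2 is used.

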**8.2 Final Inclusion**

The final inclusion will be determined after the bacteriological result of the BAL becomes available. A sheet for final inclusion, including bacteriological information and a copy of the informed consent is faxed to the principal investigator.

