**8.3 Randomisation**

Is carried out in the final inclusion. It will be performed by the main investigator centre using a pre-defined centre randomization table. The assigned treatment arm is communicated by fax between 8 a.m. and 12 p.m., Monday to Friday and at the latest by D5.

1. **Methodology**

- **Pre-inclusion**
- verification of the criteria for inclusion (except bacteriological data) and exclusion
- realization of the BAL
- realization of 3 blood cultures
- simplified acute physiologic score: SAPSIIS II (Appendix VIII)(Appendix IX) Mc Cabbe score - score of organ failure (ODIN: Appendix X)
- -score of organ failure related to sepsis (SOFA: Appendix V)
- **Inclusion**
- verification of the bacteriological criteria for inclusion.
- **D0 of treatment**
- SAPS II (Appendix VIII) score
- score of organ failure (ODIN: Appendix X)
- score of organ failure related to sepsis (SOFA: Appendix V)
- **D1 of treatment**
- SAPS II (Appendix VIII) score
- score of organ failure (ODIN: Appendix X)
- score of organl failure related to sepsis (SOFA: Appendix V)
- rectal swabs
- **D4 of treatment**
- **decrease of dosages of beta-lactam - interim evaluation**

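### A patient who has already failed can still be randomised on D4–D5, and failures before J9, which duration cannot cause, draw the arms together in an equivalence trial

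*Protocol*

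**What the plan says.** All references are to the protocol, which writes treatment days as either J or D, counted from the start of antibiotics (J0).

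- **When failure becomes final.** Section 7.2.1: "If failure is diagnosed, regardless of the day (After D3 of treatment), the patient is assessed as failure in the final evaluation at D21". Death is a separate component with no start day: "Death for what ever reason during the protocol".
- **When treatment starts.** Under section 5.1, patients with the Appendix III severity criteria are treated immediately after the BAL, before its result. For them, "the patient will be included in the study as long as the treatment is not changed after the results of the sensitivity".
- **When the arm is assigned.** Section 8.2: "The final inclusion will be determined after the bacteriological result of the BAL becomes available". Section 8.3 places randomisation at that step; the arm is sent by fax between 8 a.m. and 12 p.m., "Monday to Friday and at the latest by D5".
- **When the arms diverge.** Section 5.2: "All patients included in the study will be treated by a combination of antibiotics during the first 5 days". Both arms then continue the beta-lactam alone. The first difference is the entry "J9 = Stop beta-lactam antibiotics in the" short arm.
- **Nearest eligibility safeguard.** Section 6.1: "The patient must be able to receive either one of the two arms of treatment defined for the study". Neither 6.1, 6.2 nor 8.2 mentions a failure criterion that has already been met.
- **Analysis.** Section 11 compares patients as randomised and accepts equivalence within 10 points on the cure rate.

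**The concern.** Two things follow from these dates.

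First, the period in which failure can become final opens on D4, while assignment may still be pending on D4 or D5. A patient treated straight after the BAL can thus have a fixed outcome before allocation. Once randomised, that patient is a failure whichever arm is drawn.

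Second, five more days of follow-up (D4 to D8) pass under identical protocol treatment. A failure in that time may say something about the disease or the drugs, but nothing about 8 versus 15 days.

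In a superiority trial such outcomes would work against the hypothesis. Here the aim is to show that the durations do not differ, so outcomes common to both arms move the result toward the conclusion sought, while the limit stays at 10 points.

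**Working it through.** **1. Can the overlap occur in ordinary running?** Appendix II has cultures read at 24 and 48 hours, and 6.1 also requires susceptibility. Take the BAL day as J0.

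- BAL on Thursday: the 48-hour reading falls on Saturday and the next fax slot is Monday, which is D4.
- BAL on Wednesday, with the result missing Friday's slot: the next slot is Monday, which is D5.

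D4 is also the protocol's own interim evaluation.

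**2. Which failure routes can be complete by D4–D5?**

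- Death, or a drug change for intolerance: largely kept out by the 6.1 requirement and by 5.1.
- Persistence of all signs with the original organism, and the SOFA increase with the same organism: both need a repeat BAL. One taken on D4 is read on D5–D6, usually after assignment.
- Septic shock or sepsis syndrome without another documented infection: 7.2.1 does not clearly tie this to a repeat BAL, so it can be met on D4–D5. This is the main route left open.

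**3. The plan's own sample size.** The row adopted in 11.2 has cure 0.80, then 0.10 and 0.20 under lost column headings, and 140 per group. I read the two figures as one-sided alpha and beta, which is an assumption.

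- Restricted variance: n = [1.2816·√(0.85·0.15 + 0.75·0.25) + 0.8416·√(2·0.80·0.20)]² / 0.10² = 143.
- Unpooled variance: n = 2·0.80·0.20·(1.2816 + 0.8416)² / 0.10² = 145.
- Stated: 140, within about 3% of each. Pre-included: 280/0.80 = 350, as stated.

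The one-sided 0.10 reading is therefore reasonable.

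**4. Dilution.** Let a share f of each arm fail before J9 regardless of arm. Then

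overall difference = (1 − f) × difference among patients still at risk at J9.

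The protocol gives no f. At 80% cure all failures in the 15-day arm total 20%, so f is at most 20%; at 90% cure it is at most 10%.

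Set the true deficit among patients still at risk to 10 points, with 80% overall cure in the 15-day arm and n = 140:

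- d = 0.10(1 − f) and p_short = 0.80 − d
- SE = √{[0.80·0.20 + p_short(1 − p_short)]/140}
- P(declare equivalence) = Φ[(0.10 − d)/SE − 1.2816]

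| f | overall difference d | SE | P(declare) |
|---|---|---|---|
| 0 | 10.0 points | 0.0514 | 10.0% |
| 5% | 9.5 | 0.0513 | 11.8% |
| 10% | 9.0 | 0.0511 | 13.9% |
| 15% | 8.5 | 0.0510 | 16.2% |
| 20% (cap) | 8.0 | 0.0508 | 18.7% |

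Section 11 judges equivalence on the odds ratio, which behaves alike. At f = 10%, cure among patients at risk is 0.889 versus 0.789 (odds ratio 0.47); overall it is 0.80 versus 0.71 (odds ratio 0.61, nearer 1).

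**5. Precision of an analysis from J9.** With equal arms, SE = √[2p(1 − p)/m], where p = 0.80/(1 − f) and m = 140(1 − f).

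| Set | p | m per arm | SE |
|---|---|---|---|
| All randomised | 0.800 | 140 | 0.048 |
| f = 5% | 0.842 | 133 | 0.045 |
| f = 10% | 0.889 | 126 | 0.040 |
| f = 15% | 0.941 | 119 | 0.031 |

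Under these assumptions the subset interval is narrower, because cure among those remaining is higher.

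**The case against.** The strongest reply is that early failures belong in the comparison. The objective concerns cure in patients treated for early-onset pneumonia, the analysis is as randomised, and both the 10-point limit and the expected 80–90% are stated on overall cure. Early failures are thus already inside the scale on which the limit was set. This stands: the as-randomised difference is not miscalculated.

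It follows that the 12%, 14% and 16% must not be read as an inflated type I error, as a reader might infer. They arise at true overall differences of 9.5, 9.0 and 8.5 points, which lie inside the protocol's own limit. Accepting equivalence there is not an error under its hypothesis.

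A second reply is that randomisation after failure will be uncommon: the window is two days, it mainly concerns immediate starters whose assignment is late, and most routes are filtered out or confirmed later. This also stands, and the protocol gives no means of counting such patients. It does not close the gap for septic shock or sepsis syndrome. Immediate starters are selected for severity, so early failure in them is plausible.

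A third reply is that the larger values of f are demanding. At f = 15% and 80% cure, three quarters of the 15-day arm's failures (15 of 20 points) must come before J9. This is fair; the figures are a range, not a forecast.

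**Conclusion.** The concern holds in a limited form. The text allows a patient who already meets a failure criterion on D4–D5 to be randomised, and nothing in 6.1, 6.2 or 8.2 clearly prevents it. Separately, all failures before J9 arise under identical regimens and reduce the trial's ability to see an effect of duration.

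The consequence is lost sensitivity. A 10-point deficit among patients for whom duration can matter appears as 8 to 10 points overall across the range of f that 80% cure permits. The chance of declaring equivalence then goes from 10% to about 12–16% for f of 5–15%, and to about 19% at the cap. This rests on the assumed f, on one-sided 0.10 read from a table with lost headings, and on 140 per group.

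A reader might also infer that equivalence should be claimed only if patients failure-free at J9 show it too. The documents do not support that. It would make the subset a co-primary test, and the trial is open with the arm known by D5, so membership depends on failures judged up to J8 with knowledge of the arm. That is selection after randomisation, suited to a supporting role only.

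**What to change.** 1. **Sections 8.2 and 8.3.** Add a check to the final-inclusion sheet that no 7.2.1 failure criterion has been met since J0. Do not randomise a patient who has met one, and state in 7.2.1 that failures count only from randomisation.
2. **Section 11.** Keep the as-randomised comparison as primary. Add a supportive comparison of D21 cure among randomised patients alive and not failed at the start of J9. It should not gate the equivalence claim. State beside it that, in an open trial, the subset depends on failure judged with knowledge of the arm, and report the number of failures before J9 by arm.

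The cost is one line on an existing form, slightly fewer pre-included patients randomised, and one extra analysis. Under the assumptions above, the supportive interval would not be wider than the primary one. No dose or treatment rule changes.
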